## Abstract

**Background:**

Patients with chronic heart failure (CHF) and patients with chronic obstructive pulmonary disease (COPD) are amenable to integrated palliative care (PC); however, despite the recommendation by various healthcare organizations, these patients have limited access to integrated PC services. In this study, we present the protocol of a feasibility prospective study that aims to explore if an “early integrated PC” intervention can be performed in an acute setting (cardiology and pulmonology wards) and whether it will have an effect on (i) the satisfaction of care and (ii) the quality of life and the level of symptom control of CHF/COPD patients and their informal caregivers.

**Methods:**

A before-after intervention study with three phases, (i) baseline phase where the control group receives standard care, (ii) training phase where the personnel is trained on the application of the intervention, and (iii) intervention phase where the intervention is applied, will be carried out in cardiology and pulmonology wards in the University Hospital Leuven for patients with advanced CHF/COPD and their informal caregivers. Eligible patients (both control and intervention group) and their informal caregivers will be asked to complete the Palliative Outcome Scale, the CANHELP Lite, and the Advance Care Planning Questionnaire at the inclusion moment and 3 months after hospital discharge.

**Discussion:**

The present study will assess the feasibility of carrying out PC-focused studies in acute wards for CHF/COPD patients and draw lessons for the further integration of PC alongside standard treatment. Further, it will measure the quality of life and quality of care of patients and thus shed light on the care needs of this population. Finally, it will evaluate the potential efficacy of the “early integrated palliative care” by comparing against existing practices.

**Trial registration:**

Current Controlled Trials ISRCTN24796028 (date of registration August 30, 2018).

## Background

According to the World Health Organization (WHO), chronic heart failure (CHF) is the first cause of death worldwide while chronic obstructive pulmonary disease (COPD) is the third one [1]. Patients with CHF/COPD face heavy physical and psychosocial burdens, comparable to cancer patients [2, 3], and whereas treatment for both diseases remains non-curative, survival rates of these patients have increased with time [4]. These patients are amenable to and can benefit from palliative care (PC) services; however, the complexity of their needs requires a more integrated approach to the provision of high-quality care [4].

Integrated PC involves bringing together administrative, organizational, clinical, and service aspects in order to achieve continuity of care between all those involved in the patient’s care network. It aims to achieve quality of life and a well-supported dying process for the patient and the family in collaboration with all the caregivers (paid and unpaid) [5, 6]. Moreover, there is ample and ever-growing empirical evidence on the benefits of integrated PC on the quality of life of patients with both malignant and non-malignant diseases with typical examples including better symptom control, less caregiver burden, fewer hospital admissions, improvement in continuity and coordination of care, cost-effectiveness, and patients dying in their preferred place [4, 7–15].

However, when compared to patients with cancer, patients with CHF/COPD are quite unlikely to receive PC services and it has been estimated that less than one out of five CHF/COPD patients has access to PC services, while for cancer, this number increases to one out of two [10, 16, 17]. The most commonly reported factors responsible for this inequity are limited PC knowledge of healthcare providers and predominant focus on standard treatment options [18–21], misperception of PC as an end-of-life care [15], complexity of prognostication [18–21], perception of CHF and COPD as “manageable” chronic diseases [22–24], and inadequate communication and collaboration between the involved medical disciplines [6, 25–27].

The nature of these inhibiting factors suggests that optimal practices will combine optimized strategies for the delivery of high-quality care vis-a-vis the efficient and effective organization of services within the local context and societal impact including optimal patient/professional experiences.

## Aim

The aim of this study is twofold: (1) to assess the feasibility of administering an early PC intervention in cardiology and pulmonology wards and (2) to measure the potential benefits of an early PC intervention in CHF/COPD patients in their QoL and satisfaction of care. Additionally, the objectives of this study are as follows:i)To identify barriers in administering an early integrated PC intervention in an acute settingii)To examine the appropriateness of the eligibility (referral) criteriaiii)To measure whether and to what extent patients and their informal caregivers share common beliefs on QoL and quality of careiv)To test the hypothesis that early integration of PC in CHF/COPD can improve QoL and quality of carev)To identify the PC needs of the targeted population

## Methodology and study design

We propose to conduct a before-after intervention study consisting of three sequential phases: baseline phase, training phase, and intervention phase. During the baseline phase, the control group will receive standard care. During the training period, the personnel will be trained on how to use and apply the “early palliative care integration” intervention. Finally, during the intervention phase, the intervention group will receive the updated care (Fig. 1).

**Fig. 1 Fig1:**
[figure not shown]
Sequence of the feasibility before-after intervention study

In both groups (control and intervention), patients and their most important informal caregiver will be asked to complete the Canadian Health Care Evaluation Project (CANHELP Lite) Questionnaire [28], the Palliative Outcome Scale (POS) Questionnaire [29], and the Advance Care Planning Questionnaire developed by the Palliative Support Team (at the University Hospital Leuven) to measure the current level of integrated PC in the following two timings: (i) inclusion moment after signing the informed consent and (ii) 3 months after inclusion (for both baseline and intervention groups). The methodology of this study was developed based on the SPIRIT guidelines.

We decided to jointly study CHF and COPD due to the fact that these two chronic, high prevalence, and non-malignant diseases share heavy physical and psychosocial symptom burden and similarly complicated disease trajectories, and currently, they are not curable [30, 31]. Moreover, there is also empirical evidence that CHF/COPD specialists share similar views on the role of integrated PC for these two diseases [32].

Currently in our hospital, the acute wards outside oncology have access to the Palliative Support Team, but they typically call for it only in the last hours (in the best case, in the last 2–3 days) of a patient’s life. The personnel of the cardiology and pulmonology wards have no training on the provision of PC.

### Inclusion criteria

#### Patients

Adult patients have been readmitted at least once within a year with a New York Heart Association (NYHA) classification of III/IV for CHF (Table 1) or with Global Initiative for Chronic Obstructive Lung Disease (GOLD) stages C/D for COPD (Table 2). These patients should have an assessed life expectancy of at least 6 months.

**Table 1 Tab1:** NYHA classification for CHF symptoms

NYHA class	Symptoms
I	Cardiac disease, but no symptoms and no limitation in ordinary physical activity, e.g., no shortness of breath when walking, climbing stairs, etc.
II	Mild symptoms (mild shortness of breath and/or angina) and slight limitation during ordinary activity
III	Marked limitation in activity due to symptoms, even during less-than-ordinary activity, e.g., walking short distances (20–100 m) Comfortable only at rest
IV	Severe limitations, experiences symptoms even while at rest, mostly bed-bound patients

*NYHA* New York Heart Association

**Table 2 Tab2:** GOLD criteria for COPD

A = low risk, low symptom burden	
• Low symptom burden (mMRC of 0–1 or CAT score < 10) and	
• FEV1 of 50% or greater (old GOLD 1–2) and low exacerbation rate (0–1/year)	
B = low risk, higher symptom burden	
• Higher symptom burden (mMRC of 2 or more or CAT of 10 or more) and	
• FEV1 of 50% or greater (old GOLD 1–2) and low exacerbation rate (0–1/year)	
C = high risk, low symptom burden	
• Low symptom burden (mMRCof 0–1 or CAT score < 10) and	
• FEV1 < 50% (old GOLD 3–4) and/or high exacerbation rate (2 or more/year)	
D = high risk, higher symptom burden	
• Higher symptom burden (mMRC of 2 or more or CAT of 10 or more) and	
• FEV1 < 50% (old GOLD 3–4) and/or high exacerbation rate (2 or more/year)	

*mMRC* Modified Medical Research Council Dyspnea Scale, *CAT* COPD assessment test, *FEV1* the amount of air a patient can force from his/her lungs in 1 s

#### Informal caregivers

Informal caregiver is defined as the proxy person who takes care and supports the patient for most of the time. This caregiver may not necessarily be a family member. They should be aged 18 or above, should be able to communicate in Dutch, and should be cognitively able to complete questionnaires.

### Exclusion criteria

A potential participant (patient or informal caregiver) who meets any of the following criteria will be excluded from participation in the study:i)Under the age of 18ii)Unable to communicate in Dutchiii)People who lack the mental capacity to complete questionnairesiv)If the surprise question “Would you be surprised if the patient died within 1 year?” is answered “Yes”

### Sample size

A convenience sample of 50 patients and 50 informal caregivers per phase (25 CHF and 25 COPD patients and their informal caregivers for the baseline phase and 25 CHF and 25 COPD patients and their informal caregivers for the intervention phase) has been set as a target based on the following rationale. We use as a reference a two-sample *t* test on the total POS scores, assuming a minimally relevant difference of 4, i.e., 10% of the best score 40, and a common standard deviation of 6, which constitutes the worst case based on previous studies [33, 34]. In order to obtain 80% power at a significance level of 5%, a total of 37 patients per group will be required. To this number, we will add a 30% attrition rate which results in 50 patients and caregivers per group. We will retrospectively compute our standard deviation with an interim analysis once three fourths of the originally planned sample size has been collected to examine whether upward revisions are required.

It is important to note that due to the shortage of studies similar to ours, attrition rates for the population of interest are not well understood. As a starting point, we have used attrition rates from integrated palliative care cancer studies and we aim to retrospectively evaluate the suitability of these rates.

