#### Data analysis

The statistical analysis will be carried out by the main researcher and will be performed using SPSS version 23.0 and Excel version 18.11 software. We will employ standard descriptive statistics for the basic characteristics of the population and the distributions of the scores of the tests (means, standard deviations, etc.). We will use *t* tests to explore the equality of means for total scores of POS and CANHELP Lite between different pairs (e.g., COPD patients vs COPD caregivers). To compare continuous variables between the different study groups, we will use Fisher’s exact tests and Mann-Whitney *U* test. Finally, we will use Mann-Whitney *U* tests and Wilcoxon signed-rank tests in order to analyze individual questions that will be treated as ordinal variables, while 95% confidence intervals will also be presented. Missing data will be included in the analysis, and their implications will be clarified.

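### The named between-phase tests carry no disease term although each phase targets equal CHF and COPD numbers; adding one is a cheap, optional gain in precision and protection against a shifting disease mix

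*Protocol article*

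**What the plan says.** The Sample size section sets a target of 50 patients per phase, split equally by disease: "25 CHF and 25 COPD patients and their informal caregivers for the baseline phase", with the same split for the intervention phase. The split "has been set as a target based on the following rationale". That rationale is a two-sample t "test on the total POS scores, assuming a minimally relevant difference of 4", together with "a common standard deviation of 6, which constitutes the worst case based on previous studies". The section does not say whether this SD is taken within one disease or across both. It concludes that "a total of 37 patients per group will be required", the two diseases counted together, and then "we will add a 30% attrition rate which results in 50 patients and caregivers per group". The SD is to be recomputed at an interim look, after three quarters of the planned sample, to decide whether to enlarge the study.

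The Data analysis section lists t tests on POS and CANHELP Lite totals for various pairs. Fisher's exact and Mann-Whitney tests are listed under the purpose "To compare continuous variables between the different study groups", and Mann-Whitney and Wilcoxon signed-rank tests for single items. No listed test is stratified by disease, and no model with a disease term is named.

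**The concern.** Disease is a design variable here: its share is planned to be the same in both phases, and it is known for every patient. It also coincides with ward, screening route and intervention team (Duration and setting, Recruitment, The intervention). A comparison that leaves it out can lose in two ways.

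- **Precision.** With equal mixes, a CHF-COPD gap in mean score does not make the phase difference vary, yet it enlarges the SD from which the standard error is computed. Intervals are then wider than they need be and the test rejects less often than its nominal level.
- **Bias.** If the patients analysed do not have the same mix in both phases, part of the disease gap enters the unadjusted phase difference. In a before-after comparison without randomisation, this confounder can be removed with data already held.

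At stake are the width of the interval and, to a lesser degree, the position of the estimate for the one comparison that has a stated power.

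**Working it through.** **Inputs from the Sample size section:** difference 4, SD 6, 80% power, 5% level (two-sided assumed), 37 per group, 50 enrolled, 30% attrition. **Assumed:** the CHF-COPD gap D in mean total POS, which the protocol does not give; range 0 to 6 points.

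**1. The plan's own figure.** The normal approximation gives n = 2(1.96 + 0.842)² × 36/16 = 35.3, so 36. The exact noncentral t gives 79.7% power at 36 and 80.8% at 37. The stated 37 reproduces.

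**2. Completers.** 50 × 0.70 = 35 per phase, with exact-t power 78.5% at SD 6. This is the baseline below. Its distance from 80% comes from the attrition allowance and is not part of this point.

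**3. Variance.** With a 1:1 mix, total variance = within-disease variance + D²/4. The standard error of the phase difference depends on the within-disease SD only; the plain t test uses the total SD. The approximate true size is 2[1 − Φ(1.96 × total SD / within-disease SD)].

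**4. Results.** Simulation with 35 per phase, the same 18/17 mix in both phases, and a true difference of 4 for power; size is from the formula in step 3. Adjusted means a linear model with phase and disease.

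If SD 6 is the within-disease SD:

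| D | Total SD | Size, unadjusted | Power, unadjusted | Power, adjusted |
|---|---|---|---|---|
| 0 | 6.00 | 5.0% | 78.5% | 78.5% |
| 2 | 6.08 | 4.7% | about 78% | about 78.5% |
| 4 | 6.32 | 3.9% | about 75% | about 78.5% |
| 6 | 6.71 | 2.8% | about 71% | about 78.5% |

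If SD 6 is the total SD over both diseases:

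| D | Within-disease SD | Size, unadjusted | Power, unadjusted | Power, adjusted |
|---|---|---|---|---|
| 0 | 6.00 | 5.0% | 78.5% | 78.5% |
| 2 | 5.92 | 4.7% | about 79% | about 80% |
| 4 | 5.66 | 3.8% | about 80% | about 83% |
| 6 | 5.20 | 2.4% | about 82% | about 89% |

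On either reading the power forgone is about 0, 1, 3 and 7 points.

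**5. Unequal mix.** Suppose completers are 20 CHF + 15 COPD in one phase and 15 + 20 in the other, with D = 4. The unadjusted difference shifts by 4 × (20/35 − 15/35) = 0.57 points, which is 0.57/4 = 14% of the minimally relevant difference. If the mix is 20 + 15 in both phases, the shift is 4 × (20/35 − 20/35) = 0.

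**6. Interim SD.** If the within-disease SD is 6 and D = 4, the pooled SD is √(36 + 4) = 6.32. The formula in step 1 then gives 2 × 7.85 × 40/16 = 39.2, so 40 per phase instead of 36. That increase would answer variance which an adjusted analysis does not carry.

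**The case against.** Much of the case on the other side stands, and it limits the point.

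- **Fixed quotas.** A reader might infer that the 25 + 25 split is guaranteed. The protocol calls it a target for a convenience sample, and the Recruitment section allows adjustments. The precision argument holds as far as the mix stays equal, and the bias argument as far as it does not. They describe different outcomes, and a disease term deals with both.
- **Disease ignored altogether.** A reader might infer this from the list of tests. The t tests are for various pairs, and the one example lies within COPD, so within-disease comparisons are not ruled out. That example sets patients against caregivers, though, not phase against phase. Separate phase comparisons of about 18 against 18 would have far less power than one adjusted analysis. Covariates are often left to a fuller document, so the point rests on the tests the article names and not on what it leaves out.
- **The 80% is wrong.** A reader might conclude this. If SD 6 is the SD over both diseases, the sample size already pays for the gap, and only power relative to a better analysis is forgone. The protocol describes 6 as a worst case, which is compatible with that reading.
- **A larger loss.** Putting the inflated SD into the usual power formula gives 77, 74 and 69% at gaps of 2, 4 and 6. That treats the phase difference as varying with the gap, which an equal mix prevents; the simulated figures are about 78, 75 and 71%.
- **Attrition by disease alone as a source of bias.** It does not bias the comparison if it is the same in both phases. Completion must differ by disease and by phase, or recruitment must be uneven.
- **No evidence of a gap.** The methodology section argues that the two diseases carry a similar burden. That supports studying them together but does not establish equal mean scores. At a gap of zero the loss is nil, and 6 points is 1.5 times the minimally relevant difference.

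**Conclusion.** The point holds as an optional improvement in efficiency and protection against bias. The stated 37 per group reproduces, and the unadjusted test does not produce excess false positives when the mix is equal. Over assumed gaps of 0 to 6 points with 35 completers per phase, the power forgone runs from nothing to about 7 points; at a gap equal to the protocol's own minimally relevant difference it is about 3. Whether the planned power also falls depends on which SD the 6 is: if within-disease, a 4-point gap takes it from 78.5% to about 75%; if pooled, it does not fall for this reason. The 0.57-point bias is an illustration that needs both a 4-point gap and a completer mix that reverses between phases. These figures rest on normal scores, equal SDs in the two diseases and the same phase effect in both.

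**What to change.** In the Data analysis section, include disease (CHF or COPD) as a fixed term in each between-phase comparison of POS and CANHELP Lite totals. Use a linear model with phase and disease in place of the plain t test, and a disease-stratified van Elteren test in place of the plain Mann-Whitney test. Report the phase effect from these analyses.

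In the Sample size section, state whether SD 6 is within-disease or pooled over both diseases, and compute the interim SD within disease so that any upward revision matches the analysis to be used.

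The cost is a few sentences and one degree of freedom, with no new data. The stratified rank test may need a short script outside the standard SPSS menus.

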### Duration and setting

The overall study is estimated to last 24 months and will be conducted in UZ Leuven in the Departments of Cardiology and Pulmonology (two nursing wards for CHF and one for COPD). We estimate 8 months duration for the baseline and the intervention phase and 3 months for the training period. An overall time delay of 25% has also been added to the timeline.

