### The intervention

After the completion of the baseline phase of the study (patients receiving standard care), the appointed intervention team for each ward will receive a training on how to apply the intervention in a 3-month period. The psychologist of UZ Leuven’s Palliative Support Care Team will be the one to train the personnel on how to apply the intervention to the experimental group. In cardiology, the assistant physicians will provide an introductory flyer for the intervention to the patient, and after the completion of this flyer, two psychologists and one psychology trainee will proceed with the implementation of the intervention. The same process will follow for the pulmonary ward, where after the introductory flyer by the assistant physicians, a specialist nurse, two ward nurses, and a spiritual counselor will proceed with the intervention.

The intervention will be based on the implementation of the early integrated palliative care planning intervention “My Wishes” (“MIJN WENSEN voor mijn Gezondheidszorg”), a content-validated communication tool for advance care planning in chronic disease developed by the Palliative Support Team in UZ Leuven (reference number 700864).

This tool addresses the wishes and needs of the patients concerning the delivery of care. It considers how the patient’s needs may be translated into treatment agreements for the present and the future taking into account the medical possibilities and limitations. MIJN WENSEN will be used as an invitation to communication and as a guide for conversations with the caregivers and for matching the current and future care with the treatment specialists. MIJN WENSEN can be also used as an informal declaration of intent, to register the patient’s indicated representative who will advocate the wishes of the patient in case she/he ever becomes unable of taking any decisions on their medical care. It can even be used as a formal declaration of intent, not only for the indication of a representative, but also the content of the treatment wishes for every type of mental incompetence.

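### The 80% power and the named tests assume independent patients; ward effects that change between phases, or deliverer effects, would make power and between-phase intervals too favourable

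*Protocol article*

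**What the plan says.** Sample size, in the protocol article, names its basis: "We use as a reference a two-sample *t* test on the total POS scores". The target difference is 4 points, set as a tenth of the best score. The spread is described as "a common standard deviation of 6, which constitutes the worst case based on previous studies". The section then concludes: "In order to obtain 80% power at a significance level of 5%, a total of 37 patients per group will be required". Attrition is then added to reach 50 per phase. The planned interim look revisits the standard deviation only.

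Duration and setting gives the units: "two nursing wards for CHF and one for COPD", with both phases run in these departments. The intervention section names those who deliver it after the baseline phase. In cardiology, "two psychologists and one psychology trainee will proceed with the implementation of the intervention"; in pulmonology, "a specialist nurse, two ward nurses, and a spiritual counselor will proceed with the intervention".

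Data analysis lists t tests for total scores, Fisher's exact and Mann-Whitney tests between study groups, and Mann-Whitney and Wilcoxon tests for single questions, where "95% confidence intervals will also be presented". No ward or deliverer term appears. Limitations gives overlapping staff as the reason for not running an RCT, but does not mention correlated outcomes.

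**The concern.** Patients treated in one ward during one phase share staff, workload and ward conditions. If those conditions shift between the phases, all patients of that ward-phase shift together, and the standard error of a t test on individual patients does not see it. In the intervention phase alone, patients may also share the person who holds the conversation, and the tool is conversation-based, so a deliverer effect is plausible.

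Either source would make the standard error of the between-phase difference in Palliative Outcome Scale (POS) total too small. The 5% test would then reject too often, intervals would cover less than 95%, and power computed with a correct standard error would fall below the stated figure. The point also bears on item 1 of the feasibility table (Table 3), which asks whether the study allows a sample size for the main trial. A standard deviation and an attrition rate alone would not show how strongly outcomes cluster.

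**Working it through.** **Inputs from the protocol.** Difference 4, SD 6, two-sided 5% (sidedness is not stated, but two-sided reproduces the figure), n = 37 per phase, three wards, and named deliverers 3 + 4 = 7.

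**Assumed inputs.** All correlations. Ward shares of 1/4, 1/4 and 1/2 (half the patients have COPD, in one ward; half have CHF, split evenly over two wards). One deliverer per patient, in the deliverer case only.

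**1. The plan's own figure.** Under independence the standard error is 6 × √(2/37) = 1.395. The noncentral t distribution with 72 degrees of freedom gives 80.8% power at n = 37 and 79.7% at n = 36. So 37 is right for its inputs, with little to spare.

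**2. Ward effects that change between phases.** Let r be the share of total variance that is shared within a ward-phase and does not carry over to the other phase. The sum of squared shares is 0.25² + 0.25² + 0.5² = 0.375. The variance of the difference, relative to independence, is

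inflation = (1 − r) + 37 × r × 0.375.

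Power uses a standard error multiplied by the square root of the inflation. Type I error is that of the plain t test, simulated with wards of 9, 9 and 19 patients; the approximation 2 × [1 − Φ(1.96/√inflation)] agrees closely.

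| r | Inflation | Power, correct SE | Type I error, plain t test |
|---|---|---|---|
| 0 | 1.000 | 80.8% | 5.0% |
| 0.01 | 1.129 | 75.9% | 6.6% |
| 0.02 | 1.257 | 71.3% | 8.0% |
| 0.05 | 1.644 | 59.7% | 12.6% |

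**3. How much depends on persistence.** Let ρ be the total ward correlation and c the fraction of the ward effect that persists from one phase to the next. Then

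inflation = (1 − ρ) + 37 × ρ × (1 − c) × 0.375.

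- Fully stable (c = 1), ρ = 0.05: inflation 0.95. The plain t test is slightly conservative (type I error about 4.4%), and power with the correct standard error rises to about 83%.
- c = 0.8, ρ = 0.05: 0.95 + 37 × 0.05 × 0.2 × 0.375 = 1.089, power about 77%.
- c = 0.8, ρ = 0.02: 0.98 + 37 × 0.02 × 0.2 × 0.375 = 1.036, power about 79%.
- c = 0: the table above. The 60% row therefore needs ρ = 0.05 with no carry-over at all, or a larger ρ with some.

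**4. Deliverer effects, intervention phase only.** With one of seven deliverers per patient, the cluster size is 37/7 = 5.29. Variance in that phase is multiplied by 1 + 4.29 × r; the inflation for the difference is the average of this factor and 1.

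| r | Factor, intervention phase | Average | Power | Type I error, plain t test |
|---|---|---|---|---|
| 0.02 | 1.086 | 1.043 | 79.1% | about 5.5% |
| 0.05 | 1.214 | 1.107 | 76.7% | about 6% |
| 0.10 | 1.429 | 1.214 | 72.8% | about 8% |

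All power figures keep 72 degrees of freedom. With three wards or seven deliverers as the real units, that is optimistic.

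**The case against.** The strongest reply is that no correlation is documented, so a loss of power is not shown. That stands. A reader might infer that the stated power and intervals are wrong as they are; the documents support only the conditional statement. With stable ward effects the plain test errs on the safe side, and with a deliverer correlation of 0.02 power is still about 79%.

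A reader might also take 80% as a ceiling. It is not one: the protocol calls SD 6 the worst case, and with SD 5.5 or 5 the same 37 per phase gives 87% or 92%. An SD of 5.35 would offset the whole inflation at r = 0.02.

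Third, the seven clusters are inferred. The intervention section appoints a team for each ward and lists its members; it never says that one person sees each patient. If the team delivers, the clusters are the two departments, which coincide with disease, and a random deliverer effect has no basis.

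Fourth, the 95% intervals are mentioned in the sentence on single questions and are not tied to the POS total. The issue reaches them only where they compare phases.

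Finally, this is a feasibility study with a convenience sample, random-effect details may sit in an analysis plan that is not shown, and the before-after design is already declared a limitation. That lowers the weight but does not remove the point: the power claim and the tests are written down, and the declared limitation does not say that error bars may be too narrow. A cluster-randomised main trial is likewise something a reader might infer from the staff overlap; the protocol speaks only of an RCT with wards from other hospitals.

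**Conclusion.** The point holds in conditional form. The figure of 37 per group is arithmetically correct, but its 80% power at SD 6 rests on an unstated independence assumption that this design gives reason to doubt. Ward-by-phase correlations of 0.01 to 0.02 would put power at about 76% to 71% and type I error at about 6.6% to 8%; 0.05 is an extreme, not an expected case. Under the one-deliverer assumption, correlations of 0.05 to 0.10 would put power at about 77% to 73%. If ward effects are mostly stable, the loss is small or absent. Because each ward contributes only one before-after change, three wards cannot give a reliable estimate of ward-by-phase variation, so no model will repair the pooled interval fully. What can be corrected is the claim made for it.

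**What to change.** - **Sample size:** say that 80% power at SD 6 assumes independent patients, and show the sensitivity range above with its assumed correlations and ward shares.
- **Data analysis:** estimate the between-phase difference in POS total with ward as a fixed factor. Show the three ward-specific before-after differences beside the pooled one, and state that the pooled confidence interval does not cover ward-by-phase variation.
- **Data collection:** record the ward, and who delivered the intervention, for each patient.
- **Feasibility table, item 1:** report any observed correlation descriptively with its confidence interval.
- **Sensitivity analysis at most:** a partially nested model with a random deliverer effect in the intervention phase only, and only if one main deliverer per patient can be identified.

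The cost is some wording, one added variable, and a less favourable power statement. Any correlation estimate will be imprecise. No extra patients are needed.

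### Fifty per group does not leave 37 evaluable after 30% attrition: 35 remain, with about 78.5% power instead of the stated 80%, a small shortfall that one restated sentence corrects

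*Protocol article*

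**What the plan says.** All the figures stand in one paragraph of the protocol article, under Sample size.

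- The target is "A convenience sample of 50 patients and 50 informal caregivers per phase", made up of 25 CHF and 25 COPD patients in each phase.
- The basis is a power calculation: "We use as a reference a two-sample *t* test on the total POS scores".
- The effect is set by "assuming a minimally relevant difference of 4, i.e., 10% of the best score 40", and the spread by "a common standard deviation of 6, which constitutes the worst case based on previous studies".
- For 80% power at a 5% significance level, "a total of 37 patients per group will be required".
- The allowance for loss follows: "To this number, we will add a 30% attrition rate which results in 50 patients and caregivers per group".
- The standard deviation is to be recomputed once three fourths of the planned sample is in, "to examine whether upward revisions are required".

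The next paragraph says that attrition in this population is poorly understood, that the rate was borrowed from cancer studies as a starting point, and that its suitability will be judged in retrospect.

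**The concern.** Attrition is the share of enrolled participants who are lost. If 30% are lost, 70% remain, so the number to enrol is the number needed divided by 0.70. Adding 30% of the needed number is a different operation and always falls short. The three printed figures (37 needed, 30% lost, 50 enrolled) cannot all hold: 70% of 50 is 35, two fewer per group than the section says are required.

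Two things are at stake, both modest. First, the power and the attrition allowance that the article states are not met together, and testing whether early palliative care improves quality of life is one of the listed objectives (Aim, objective iv). Second, this study is meant to inform a later trial. Table 3 asks whether it allowed a sample size calculation for the main trial, and Post-feasibility study planning foresees a randomised trial. The same inflation step could be carried forward.

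**Working it through.** **Inputs (protocol article, Sample size):** difference 4 points on the total POS score; common standard deviation 6; power 80%; significance level 5%; 37 required per group; attrition 30%; 50 enrolled per group. Sidedness is not stated. Two-sided is assumed because it reproduces 37; a one-sided test would need about 29.

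**1. Reproduce the 37.**
- Standardised difference: 4/6 = 0.667.
- Normal approximation: n = 2 × [6 × (1.960 + 0.842)/4]² = 35.3, so 36 per group.
- Two-sample t test (noncentral t): n = 36.3, so 37 per group. This matches the article.

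**2. Enlarge for 30% attrition.**
- Correct form: n/(1 − attrition) = 37/0.70 = 52.9, so 53 per group. Because 53 is odd, equal CHF and COPD halves need 54.
- Multiplying instead: 37 × 1.30 = 48.1, so 49. Rounding on to 50 would suit the 25 + 25 split, but that last step is an inference.
- Starting from unrounded requirements does not rescue 50: 36.3/0.70 = 51.9 (52) with the t test, and 35.3/0.70 = 50.5 (51) with the normal approximation.

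**3. What 50 gives.**
- Evaluable at 30% loss: 50 × 0.70 = 35 per group.
- Largest loss that still leaves 37: 1 − 37/50 = 26%.

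| Evaluable per group | Attrition from 50 | Power, t test | Power, normal approximation |
|---|---|---|---|
| 37 | 26% | 80.8% | 81.8% |
| 36 | 28% | 79.7% | 80.7% |
| 35 | 30% | 78.5% | 79.6% |

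- Difference detectable with 80% power at 35 per group: 4.08 points, against the planned 4.

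**4. Losses treated as random.** If each patient independently has a 30% chance of loss (an assumption), the power averaged over the number retained is 78.2% with 50 enrolled per group and 80.6% with 53. The chance that a group retains at least 37 is about 33% with 50 and 58% with 53.

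**The case against.** The strongest case on the other side accepts the arithmetic and disputes its weight.

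- **The loss is tiny.** It is 1.5 points of power with the t test and 0.4 with the normal approximation. This stands, and it limits how strongly the point can be put.
- **The inputs are less certain than the gap.** The article calls a standard deviation of 6 a worst case. With 35 per group, a standard deviation of 5.88 already gives 80.1% power. This stands conditionally, since the studies behind the 6 are not at hand.
- **There is no cliff at 26%.** The unrounded requirement is 36.3, and 28% attrition still gives 79.7% power. This stands: 26% is the limit for keeping 37 evaluable, not a point where power collapses.
- **The section describes what it did.** It speaks of adding the rate to 37, and 37 plus 30% is 48.1, which can be rounded to 50. That explains where 50 probably came from. It does not make 50 sufficient for a 30% loss.
- **The target is provisional.** It is a convenience sample in a feasibility study, the attrition rate is a starting point, and an interim check may raise the numbers. The provisional status stands. The check does not cure the slip, because it concerns the standard deviation; attrition is to be judged only in retrospect.

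A reader might infer that the study is underpowered or that its design fails at the planned attrition. The documents do not support that: on their own inputs, power at 30% loss stays within two points of the stated value.

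**Conclusion.** The stated figure is wrong as written, and the consequence is small. Thirty-seven evaluable per group with 30% attrition requires 53 enrolled (54 with equal disease halves), not 50. At 50 enrolled and 30% lost, 35 per group remain and power is about 78.5% instead of 80%; 37 evaluable are kept only up to 26% attrition. Nothing else in the article corrects this.

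The result rests on a two-sided t test, the article's own difference of 4 and standard deviation of 6, and attrition read in its usual sense as a share of those enrolled. That 50 arose from multiplying by 1.30 is a likely explanation, not something the article states; the mismatch does not depend on it.

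It would also go too far to conclude that enrolment must be raised. In a feasibility study with an admittedly uncertain attrition rate, a correct statement of what 50 provides is enough.

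**What to change.** Keep 50 per phase and replace the attrition sentence with figures that agree, for example: *50 per phase leaves 35 evaluable at 30% attrition (about 78.5% power for a difference of 4, SD 6), or 37 evaluable (about 81% power) at up to 26% attrition.* State that the test is two-sided, and use n/(1 − attrition) when the later randomised trial is sized.

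The cost is one sentence and a slightly less favourable stated power. Recruitment and timeline do not change. The alternative of raising the target is not needed to correct the error. If it were preferred, the equal CHF/COPD split would call for 54 per phase, which is 2 × 4 = 8 more patients in total, plus their caregivers.
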